**Figure 1 f1:**
[figure not shown]
Study overview. CRC, metastasized colorectal carcinoma; CC-3, bispecific CD276xCD3 antibody; SRC, safety review committee; MTD, maximum tolerated dose; RP2D, recommended phase II dose.

**Figure 2 f2:**
[figure not shown]
Dose-escalation part. **(A)** Dosing. First patient (Pat 1) receives 50 µg weekly over 16 weeks. During 3 weeks after first application, dose-limiting toxicity (DLT) will be evaluated and the dose level (DL) for the next patient (Pat 2) will be determined by safety review committee (SRC). Repetition of SRC-guided accelerated dose escalation with following patients until occurrence of DLT, AEs ≥2, or decision of SRC, in patient X (Pat X). Switch to 3 + 3 design with last DL before reaching a criterion (Pat X-1) being used as a priming dose (green frame) for the first application, followed by the DL at which the stopping criterion was observed (Pat X) in subsequent applications. When last patient of each cohort has been observed for 21 days after application of target dose, DLT will be evaluated and the dose level for next cohort of at least three patients is determined by SRC. * up to two additional subjects may be enrolled at each DL; ** up to six additional subjects may be enrolled at each DL; *** SRC may decide to add one additional priming dose, so that target dose is reached at week 3 and DLT evaluation period thus prolonged until end of week 4 (dashed lines). **(B)** Flowchart. If no DLT, AEs grade ≥2, or respective decision of SRC occurs, dose levels may be incremented by up to 100% during accelerated dose titration, enabling a rapid increase up to the maximum target dose after a potential minimum of eight patients. After switching to 3 + 3 design, the number of patients per cohort depends on occurrence of DLT, until maximum tolerated dose (MTD) is reached.

### Justification of starting and target dose

2.4

The definition of the starting dose of 50 µg for CC-3 was based on preclinical data derived from CC-3 dose titrations of *in vitro* T-cell activation and cytokine release, in comparison with pharmacokinetic (PK) data from a clinical study with CC-1 (a bsAb with PSMAxCD3 specificity of otherwise identical format), as well as on clinical experience and clinical studies with MGD009 [a bsAb with CD276xCD3 specificity in a different format (34)] and CD20xCD3 bsAb (35). The maximum dose of 4,000 µg of CC-3 was derived from an *in vivo* model with humanized NOD scid gamma (NSG) mice, in which repetitive dosing with 1.4 µg of CC-3 achieved an eradication of established flank tumors. This dose corresponds to approximately 4,000 µg per week in humans.

### Inclusion criteria

2.5

Patients must meet the following criteria prior to treatment in the CC-3 study:

Provision of a written informed consent;Patient is able to understand and comply with the protocol for the duration of the clinical trial including undergoing treatment and scheduled visits and examinations;Progressive metastatic CRC. Patient must have received three or more prior systemic therapy regimens in the metastatic situation, including FOLFOX, FOLFIRI, FOLFOXIRI, TAS-102, or regorafenib if applicable, in combination with anti–vascular endothelial growth factor (VEGF/VEGFR) monoclonal antibody (mAb) and anti-EGFR mAb in rat sarcoma (RAS) wild-type and left-sided tumors. Exceptions:

  ○ Patients with microsatellite instability (MSI)–high/deficient DNA mismatch repair (MMR) tumors should have received ICI therapy and at least two further therapy regimens of those stated above;  ○ Patients with V-Raf Murine Sarcoma Viral Oncogene Homolog B (BRAF)V600E mutation should have received cetuximab in combination with encorafenib in second- or third-line treatment; and  ○ Patients who are considered unsuitable or unwilling to receive further available standard therapy.At least one measurable lesion that can be accurately assessed at baseline by computed tomography (CT) or magnetic resonance imaging (MRI) and is suitable for repeated assessment per RECIST 1.1;

Eastern Cooperative Oncology Group (ECOG) performance status ≤2;Age ≥18 years, no upper limit;Female patients of childbearing potential (FCBP) and male patients with partners of child bearing potential who are sexually active must agree to the use of two effective forms (at least one highly effective method) of contraception. This should be started at signing of informed consent and continue throughout the period in which study treatment is taken and for 2 months after the last dose of CC-3;For FCBP, two negative pregnancy tests (sensitivity of at least 25 mlU/mL) prior to first application of CC-3;All subjects must agree to refrain from donating blood while on the study drug and for 2 months after the last dose of CC-3;Adequate bone marrow, renal, and hepatic function defined by laboratory tests within 14 days prior to clinical treatment:

  ○ Hemoglobin ≥9 g/dL (transfusion of packed red blood cells prior to enrollment allowed);  ○ Neutrophil count ≥1.500/mm³;  ○ Platelet count ≥75.000/µL;  ○ Serum creatinine ≤1.5 mg/dL or creatinine clearance ≥60 mL/min;  ○ Hepatic function of patients without current hepatic metastasis:  ◼ Bilirubin ≤1.5 × upper limit of normal (ULN); in case of known Gilbert syndrome, higher values are allowed if due to increase of indirect bilirubin  ◼ Alanine aminotransferase (ALT) and aspartate aminotransferase (AST) ≤2.5 × ULN.  ○ Hepatic function of patients with current hepatic metastasis:  ◼ Bilirubin ≤2.5 × ULN;  ◼ ALT and AST ≤5 × ULN.

### Exclusion criteria

2.6

Patients fulfilling any of the following criteria cannot be enrolled in the CC-3 trial:

Other malignancy requiring treatment within the last year except: adequately treated non-melanoma skin cancer and low-grade non-muscle invasive papillary bladder cancer;Concurrent or previous treatment within 30 days before the first CC-3 application in another interventional clinical trial with an investigational anticancer therapy;Persistent toxicity (≥grade 2 according to CTCAE version 5.0) caused by previous cancer therapy, excluding alopecia and neurotoxicity;• Clinical signs of active infection (>grade 2 according to CTCAE version 5.0);Known cerebral/meningeal manifestation of CRC;History of human immunodeficiency virus infection;Active or chronic viral hepatitis (hepatitis B or hepatitis C);Ongoing autoimmune disease;History of relevant central nervous system (CNS) pathology or current relevant CNS pathology (e.g., seizures, paresis, aphasia, cerebrovascular ischemia/hemorrhage, severe brain injuries, dementia, Parkinson’s disease, cerebellar disease, organic brain syndrome, psychosis, and coordination or movement disorder);Therapeutic anticoagulation therapy;Major surgery within 4 weeks of starting study treatment. Patients must have recovered from any effects of major surgery;Patients receiving any systemic chemotherapy, mAb, or radiotherapy within 2 (for mAb 4) weeks prior to study treatment or a longer period depending on the defined characteristics of the agents used;Heart failure New York Heart Association (NYHA) classification III/IV;Severe obstructive or restrictive ventilation disorder;Intolerance or hypersensitivity to CC-3 (including any excipient present in CC-3) or other immunoglobulin drug products;Live and live-attenuated vaccination 30 days prior to treatment;Pregnant or breastfeeding women;Current ileus with severely altered gastrointestinal function.

### Treatment/study distribution

2.7

The study will be divided into two parts. In both, patients receive CC-3 monotherapy as short-term infusion over 3 h once per week, with up to 16 applications per patient if no criterion for treatment termination is met (see treatment schedule in **Figure 3**). Depending on the tolerability of the first three doses, which are always applied in the inpatient setting, further applications may be applied in an outpatient setting at the investigator’s discretion. The treatment phase is followed by a treatment free period of 8 weeks with weekly follow-up visits; the end of safety follow-up visit is thus scheduled for week 24. The duration of the trial for each patient is expected to be 6 months. Thereafter, patients will receive routine treatment by the admitting oncology center. Long-term follow-up data will be collected by telephone calls outside the clinical trial protocol for 3 years. In case of a confirmed benefit of the CC-3 treatment within the clinical trial, a continuation of CC-3 treatment outside the study is possible. A possible continuation will be based on a case-by-case decision by the investigator and the SRC.

**Figure 3 f3:**
[figure not shown]
Study schedule. Screening ≤28 days. **(A)** Accelerated titration phase. Dose level in the accelerated titration phase is fixed in each patient and is applied once per week. Dose increase in the next patient can be up to 100% based on safety, PK, and PDK data. For the first application of CC-3 at visit T1V1, patients must be treated as in-patients and followed for safety reasons for at least 48 h Subsequent applications of CC-3 are conducted as in-patient with one overnight stay. If well tolerated and upon medical evaluation, the following doses may be administered in an out-patient setting. In-patient treatment (hospitalization for one night) is feasible and allowed for any subsequent CC-3 treatment. **(B)** Standard titration phase. Dose level at which no AE ≥2 and no DLT was observed during the accelerated titration phase is used as priming dose in the first cohort of enrolled patients (green frame). At T2V1, patients receive DL at which stopping criterion was observed in accelerated titration phase. SRC can decide to introduce an additional second (higher) priming dose (yellow frame) to be applied at T2V1, and dose escalation is conducted at T3V1. For the first application of CC-3 at visit T1V1, patients must be treated as in-patients and followed for safety reasons for at least 48 h Subsequent applications of CC-3 are also conducted as in-patient visits with a single overnight stay. After application of at least three target doses was well tolerated and upon medical evaluation, the following target doses may be administered in an out-patient setting. In-patient treatment (hospitalization for one night) is still feasible and allowed for any subsequent CC-3 treatment. EOT, end of treatment; FU, follow-up; EOS, end of study; S, screening; T, treatment cycle; V, visit.

#### Dose-escalation part

2.7.1

Initially, dose escalation will be conducted using an accelerated titration design with single-patient cohorts for each DL. Up to two additional subjects may be enrolled at each DL in case more PK, pharmacodynamic (PDK), or safety data are deemed necessary by the SRC. A staggered enrollment design is used for each DL, with a minimum observation period of 72 h between two consecutive subjects’ first doses with the same DL. This is considered sufficient to identify CRS as most critical toxicity. Every patient receives a fixed dose, starting with 50 µg in the first cohort. Subsequent doses are determined by the SRC based on PK, PDK, and safety data obtained with the last DL over an observation period of 21 days, during which DLT evaluation is conducted. This accelerated phase will be replaced by a standard 3 + 3 design in case of

any AE grade ≥2 (except AEs unequivocally due to underlying disease or an extraneous cause);occurrence of DLT;DL ≥800 µg; anddecision of SRC based on PK, PDK, and safety data.

In the standard titration phase of the dose-escalation part, the last DL safely applied prior to termination of the accelerated phase is used as priming dose upon first application, followed by the DL at which the stopping criterion was observed in week two and thereafter. Based on PK, PDK, and safety data, the SRC may decide to introduce an additional intermittent priming dose at week 2, in which case the target dose will be applied at week 3. At least three patients are treated per cohort, following a rule-based 3 + 3 design. Up to a maximum of nine patients per cohort may be enrolled if more PK, PDK, or safety data are deemed necessary by the SRC. After completion of the first cohort’s DLT evaluation period (21 days after application of the target dose to the last patient), the DL for the next cohort will be determined by the SRC. This will be done considering all AEs and DLTs as well as PK, PDK, and safety data. The DL can be increased up to 100% of the previous dose. The priming dose applied in the first cohort will further be given at week 1 of every consecutive cohort, followed by the target dose at week 2 or 3, depending on whether the SRC deemed an intermittent priming dose necessary at week 2 (**Figure 2A**).

For instance, example 1 (a conservative example) as shown in **Table 1**—(i) a 50% dose increase between cohorts, (ii) one patient treated per cohort in the accelerated titration phase (three cohorts in total), (iii) six patients per cohort in the standard titration phase (10 cohorts in total), (iv) a starting dose of 50 µg, and (v) a maximum tested dose of 4,000 µg—requires a total number of 63 patients in the dose-escalation part.

**Table 1 T1:** Example 1 (a conservative example) of target dose levels in the dose-escalation part.

Level	D1	D2	D3	D3	D4	D5	D6	D7	D8	D9	D10	D11	D12
Cohort	1	2	3	4	5	6	7	8	9	10	11	12	13
Dose (µg)	50	75	113	113*	169	253	380	570	854	1,281	1,922	2,883	4,000
Assumed number of patients per cohort	1	1	1	6	6	6	6	6	6	6	6	6	6
Phase	A	A	A	S	S	S	S	S	S	S	S	S	S

*Standard titration phase is started with new cohorts of initially up to three patients. Treatment schedule is altered to introduce a priming dose on T1V1, leading to application of target dose on T2V1 and consecutive treatment das; A, accelerated titration phase (light gray); S, standard titration phase (dark gray).

Example 2 (a progressive example) as shown in **Table 2**—(i) a 100% dose increase between cohorts, (ii) one patient treated per cohort in the accelerated titration phase (four cohorts in total), (iii) upon a DL of ≥ 800 µg of three additional cohorts with three patients each, (iv) six patients treated in the last cohort of the standard titration phase, (v) a starting dose of 50 µg, and (vi) a maximum tested dose of 4000 µg—requires a total number of 19 patients in the dose-escalation part.

**Table 2 T2:** Example 2 (a progressive example) of target dose levels in the dose-escalation part.

Level	D1	D2	D3	D4	D5	D6	D7	D8
Cohort	1	2	3	4	5	6	7	8
Dose (µg)	50	100	200	400	800	1,600	3,200	4,000
Assumed number of patients per cohort	1	1	1	1	3	3	3	6
Phase	A	A	A	A	S	S	S	S

A, accelerated titration phase (light gray); S, standard titration phase (dark gray).

In case AE-fulfilling criteria for DLT occur, additional patients are enrolled into the cohort. If two patients experience DLT, then the dose is de-escalated to the previous lower DL that was formerly considered to be safe, and, further, patients receive this lower DL until a total of six patients have been treated or further DLTs develop. If two of the four or two of the six patients experience a DLT, then the DL will be de-escalated to the next lower DL formerly considered to be safe, and patients will receive this lower DL until a total of six patients have been treated (**Figure 2B**). MTD is defined as the DL at which none or one patient experienced a DLT. Once the MTD has been defined, the dose-escalation part of the study is terminated and the dose-expansion part commences.

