### Study approach

2.3

This FIH study will consist of two parts: a dose-escalation part comprising an accelerated titration phase in which the dose level (DL) is fixed for the individual patient but may increase with each patient by up to 100%, depending on safety considerations judged by an SRC. In case of CC-3–induced adverse events (AEs) ≥grade 2 according to Common Terminology Criteria for Adverse Events (CTCAE) version 5.0, dose-limiting toxicity, reaching a DL of ≥800 µg or SRC decision, this accelerated titration phase will be switched to a standard 3 + 3 dose–escalation design. At this stage, dosing will be split in a priming dose (last DL of the accelerated titration part with no AE ≥2 and no DLT) and a target dose (DL at which the stopping criterion was observed that terminated the accelerated titration part). Three patients will be enrolled in this first cohort. If one of these three develops DLT, then three additional patients will be recruited into the cohort. If two patients develop DLT, then the dose is de-escalated to the last DL considered as safe. If no patient of this cohort experiences DLT, then the next DL will be determined by the SRC and applied to a second cohort. This will again consist of three patients and follow the same DLT considerations as the previous cohort. This will be repeated until MTD is determined, with MTD defined as no more than one of the six patients experiencing DLT. Once the MTD is determined, dosing will be fixed at this level. Then, further patients will be recruited until 20 patients altogether have received CC-3 at the MTD. This dose-expansion part will serve to confirm the RP2D and to detect first signs of clinical efficacy (see also **Figures 1**, **2**).

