#### Dose-expansion part

2.7.2

After the dose-escalation part has been terminated, additional patients are treated until a total of 20 patients have received the DL defined as the MTD. During the dose-expansion part, patients can be treated simultaneously. Prior to the start of the dose-expansion part, a substantial amendment including the applied DLs will be submitted to the regulatory authorities.

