### Safety/dose-limiting toxicity

2.9

Toxicity will be graded according to the National Cancer Institute CTCAE (v5.0) and the CRS grading system by Lee et al. (36). All AEs and SAEs will be documented and reported according to good clinical practice guidelines. Furthermore, we will report on AESIs, which include occurrence of CRS, infusion-related reactions upon study drug administration and drug induced liver injury (DILI). These AESIs will be monitored closely and included in patient safety narrative reports to the data safety monitoring board (DSMB).

DLT is defined as any AE grade ≥3 that the investigator considers to be at least possibly related to study treatment and occurring within the DLT safety period (from first study drug treatment to day 21 or 28, respectively, if an additional intermittent priming dose is given) with few exceptions. Notably, grade ≥3 CRS lasting less than 48 h, grade ≥3 nausea, vomiting or diarrhea in patients who have not received optimal antiemetic or antidiarrheic treatment, as well as isolated ≥3 laboratory abnormalities resolving within 7 days and without clinical sequelae are not considered a DLT. Likewise, liver toxicity caused by obstruction, metastasis, or infection; grade ≥3 transaminitis or direct hyperbilirubinemia for <4 days; grade 3 fatigue for ≤5 days; grade 3 infusion reaction resolving within 8 h; nor grade 3 but adjustable (i.e., not refractory) arterial hypertension are not considered a DLT.

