### SRC and DSMB

2.10

Trial conduct will be overseen by an SRC composed of at least three members, including the coordinating investigator and a representative of the sponsor. It receives reports routinely 21 days after first dose of CC-3 of each single patient in the accelerated titration phase and as soon as three patients per cohort have completed the DLT evaluation period of 21 days after target dose application in the standard titration phase. The SRC assesses all available data on safety, PK, and PDK and determines the dose for the next cohort.

The DSMB is composed of three independent experts assessing study progress and safety data. It receives reports routinely after the end of the accelerated titration phase, after the end of the standard titration phase, upon request by the SRC, or in case of occurrence of DLT.

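### The fixed week 1 priming dose is not limited to escalation, so read literally it exceeds the target dose once the target is de-escalated below the original priming level

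*Protocol article*

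**What the plan says.** All references are to the protocol article. Call the level that ends the accelerated phase X.

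- **Priming (2.7.1).** In the 3+3 phase, "the last DL safely applied prior to termination of the accelerated phase is used as priming dose upon first application". That is X-1. From week 2 the first cohort receives X. For later cohorts, "The priming dose applied in the first cohort will further be given at week 1 of every consecutive cohort". The SRC may add a second priming dose, which the Figure 3 caption describes as higher. No text shown lowers or drops the first one.
- **De-escalation (2.7.1).** After two DLTs the target goes back to the preceding level, and "patients receive this lower DL until a total of six patients have been treated or further DLTs develop".
- **MTD.** Section 2.7.1: "MTD is defined as the DL at which none or one patient experienced a DLT". Section 2.3: "with MTD defined as no more than one of the six patients experiencing DLT".
- **DLT window (2.9).** It runs "from first study drug treatment to day 21 or 28"; the longer limit applies when an extra priming dose is given.
- **Oversight.** The SRC assesses the available data and "determines the dose for the next cohort" (2.10). The DSMB receives a report when a DLT occurs (2.10). Before expansion, "a substantial amendment including the applied DLs will be submitted to the regulatory authorities" (2.7.2).

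**The concern.** The priming rule is absolute, while the target can move down as well as up. X-1 is chosen for priming because it was given safely in the accelerated phase, to one patient or at most three. If X-1 later produces two DLTs as a target dose, that justification is gone, yet the written rule still makes it the first dose for new patients.

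Two things would follow on that branch:

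- Step-up dosing of a CD3 bispecific would be reversed, although the article treats cytokine release syndrome as the most critical toxicity (2.7.1).
- Because the DLT window opens at the first dose, a DLT caused by the X-1 priming dose would be charged to X-2. That pushes the selected MTD downward.

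The same holds for every de-escalated cohort below X-1, not only the one at X-2. Each such level may take six patients, and 2.7.1 allows up to nine per cohort.

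**Working it through.** **1. The ladders reproduce.** Table 1: 50 × 1.5 = 75; 75 × 1.5 = 112.5, shown as 113; patients 3×1 + 10×6 = 63, as stated. Table 2: 50, 100, 200, 400, 800 by doubling; patients 4×1 + 3×3 + 6 = 19, as stated.

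**2. The branch is reachable.** Two DLTs at X move the target to X-1. Under both MTD definitions, a level with two DLTs cannot be the MTD. So if X-1 also reaches two DLTs and a lower level exists, the target has to go to X-2. This is an inference from those rules. It does not use the 2.7.1 sentence about two of four or two of six patients, which can be read in more than one way. X-2 exists only if the switch occurs at the third level or later.

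**3. Week 1 dose against target, read literally.**

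| Target level | Table 1, switch at 113 µg (priming 75) | Table 2, switch at 800 µg (priming 400) |
|---|---|---|
| X | 75 / 113 = 0.66 | 400 / 800 = 0.5 |
| X-1 | 75 / 75 = 1.0 | 400 / 400 = 1.0 |
| X-2 | 75 / 50 = 1.5 | 400 / 200 = 2.0 |
| X-3 | no such level | 400 / 100 = 4.0 |

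One step down gives equality, which is workable. The inversion starts at the second step.

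**4. How often (DLT rates are assumptions; the article gives none).** Patients are taken as independent.

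- X rejected in a 3+3: 1 − [(1−p)³ + 3p(1−p)²·(1−p)³].
- X-1 rejected: P(≥2 DLTs among n new patients) = 1 − (1−p)ⁿ − np(1−p)ⁿ⁻¹. Here n = 6 if no accelerated-phase patient at X-1 counts toward the six, n = 5 if one counts, and n = 3 if three count (2.7.1 allows up to two additional subjects per level). Those who count are taken as DLT-free.

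| Assumed rate at X / X-1 | X rejected | X-1 rejected, n = 6 / 5 / 3 | Both, n = 6 / 5 / 3 |
|---|---|---|---|
| 10% / 5% | 0.0939 | 0.0328 / 0.0226 / 0.0072 | 0.0031 / 0.0021 / 0.0007 |
| 20% / 10% | 0.2914 | 0.1143 / 0.0815 / 0.0280 | 0.0333 / 0.0237 / 0.0082 |
| 30% / 20% | 0.5057 | 0.3446 / 0.2627 / 0.1040 | 0.1743 / 0.1329 / 0.0526 |

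These figures are for the direct route, with X rejected in the first 3+3 cohort. Routes that first go above X and come back are left out.

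**5. Effect on X-2, as an upper bound.** Rejection of X-2 is P(≥2 of 6). At assumed X-2 rates of 2.5%, 5% and 10% it is 0.0088, 0.0328 and 0.1143. If the single X-1 first dose carried the whole X-1 rate (5%, 10%, 20%), it would be 0.0328, 0.1143 and 0.3446. The X-1 rate arises from repeated weekly dosing, so the true increase would be smaller. The article gives no basis for a central estimate.

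**The case against.** The best reply is context. The priming sentence follows directly on the text about raising the dose and describes moving forward through cohorts. De-escalation comes later in 2.7.1, where added patients fill up a lower level and are said to receive that lower level; they are not called a consecutive cohort. A priming level defined by its safety would, in substance, no longer qualify after two DLTs. The article condenses a full protocol, and the escalation figures are not shown; either may settle the matter. By the time X-2 is opened at least four DLTs have occurred (two at X, two at X-1). The SRC would have reviewed them, and the DSMB, which receives a report on DLTs, advises on altering or stopping the trial (Discussion).

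Much of this stands. It makes harm unlikely and keeps the point minor. It does not remove it: the sentence covers every later cohort without qualification, the only stated change to priming is an addition, and the SRC would be departing from a written rule rather than following one. The complaint is about how far a stated rule reaches, not about a detail left to the full protocol.

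A reader might go further and infer that the trial plans to give patients a dose already found toxic. The documents do not support that, because the sentence may well be meant for escalation only.

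**Conclusion.** The point holds as a minor drafting fault. Read literally, the week 1 dose exceeds the target in each de-escalated cohort below X-1: 150% of target on the Table 1 example, 200% on Table 2, and 400% on Table 2 after one more rejected level. The chance of reaching X-2 is about 0.07–0.3%, 0.8–3.3% or 5–17% under the three assumed pairs of DLT rates, and nil if the switch occurs at the first or second level. Confidence is medium, because the full protocol and the figures are not shown.

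Three stronger inferences are not supported:

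- That a single step down is already faulty: there the priming dose equals the target.
- That X-2 would be wrongly rejected as often as 34.5% of the time: that figure is a ceiling, at the highest assumed rates, and includes the 11.4% expected from X-2 itself.
- That the 20 patients treated at the MTD would all be exposed: the amendment listing the applied levels comes before expansion and gives a further chance to correct the dose.

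**What to change.** Add to the priming sentence in 2.7.1: *The week 1 dose never exceeds the current target dose; if the target is de-escalated below the original priming level, the priming dose is lowered to the target dose or to a lower level already given safely.* If the existing sentence is meant for escalating cohorts only, it should also say so.

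With the cap set to the target, the week 1 dose at X-2 becomes 50 instead of 75 µg (Table 1) and 200 instead of 400 µg (Table 2), and the ratio to target never exceeds 1. The cost is one sentence. No patients are added, and the main escalation path, endpoints and sample size are unchanged.

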**Methods and analysis:**

This first-in-human clinical study is planned as a prospective multicenter trial, enrolling patients with metastatic CRC after three lines of therapy. During the dose-escalation part, initially, an accelerated titration design with single-patient cohorts is employed. Here, each patient will receive a fixed dose level (starting with 50 µg for the first patient); however, between patients, dose level may be increased by up to 100%, depending on the decision of a safety review committee. Upon occurrence of any adverse events (AEs) grade ≥2, dose-limiting toxicity (DLT), or reaching a dose level of ≥800 µg, the escalation will switch to a standard 3 + 3 dose design. After maximum tolerated dose (MTD) has been determined, defined as no more than one of the six patients experiencing DLT, an additional 14 patients receive CC-3 at the MTD level in the dose-expansion phase. Primary endpoints are incidence and severity of AEs, as well as the best objective response to the treatment according to response evaluation criteria in solid tumors (RECIST) 1.1. Secondary endpoints include overall safety, efficacy, survival, quality of life, and pharmacokinetic investigations.

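### The MTD definition omits 'highest' and also ends escalation, so a 1-of-6 cohort literally stops the trial with the next dose untested, contrary to Table 1

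*Protocol article*

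**What the plan says.** The MTD is defined in three places of the protocol article.

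- Abstract, Methods and analysis: "After maximum tolerated dose (MTD) has been determined, defined as no more than one of the six patients experiencing DLT".
- Section 2.3, Study approach: "This will be repeated until MTD is determined, with MTD defined as no more than one of the six patients experiencing DLT".
- Section 2.7.1, Dose-escalation part: "MTD is defined as the DL at which none or one patient experienced a DLT".

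Section 2.7.1 then attaches the consequence: "Once the MTD has been defined, the dose-escalation part of the study is terminated and the dose-expansion part commences".

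Section 2.3 gives the cohort rules. For one DLT in the first three patients: "If one of these three develops DLT, then three additional patients will be recruited into the cohort". For none: "If no patient of this cohort experiences DLT, then the next DL will be determined by the SRC and applied to a second cohort". Two DLTs lead to de-escalation. Section 2.7.1 adds that two DLTs in four or in six patients also lead to the next lower level, which is then filled to six.

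Two worked examples follow in section 2.7.1. Table 1 has three single-patient cohorts and ten standard-phase cohorts of six, running from 113 µg to 4,000 µg. Table 2 has four single-patient cohorts, then cohorts of three at 800, 1,600 and 3,200 µg, and six patients at 4,000 µg.

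**The concern.** The definition does two jobs. It names the dose to carry forward, and it is the condition that stops escalation. For the second job, 'at most 1 of 6' without 'highest' is too weak, because a well-tolerated level far below the true limit meets it as soon as six patients have been treated there.

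The outcome at issue is 1 of 6. Section 2.3 enlarges a cohort with 1 of 3 to six patients but states escalation only for a cohort with no DLT. If none of the three added patients has a DLT, the only stated rule that the result matches is the stopping definition.

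The MTD fixes the dose for the expansion to 20 patients and supports the recommended phase II dose. The review by the data safety monitoring board and the amendment planned before expansion can check the chosen dose, but neither tests a higher level that was skipped.

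**Working it through.** **1. The plan's own totals.** Table 1: 3 × 1 + 10 × 6 = 63 patients. Table 2: 4 × 1 + 3 × 3 + 6 = 19. With the 14 further expansion patients named in the abstract, 63 + 14 = 77, the total in section 2.11. All three reproduce, so the planned total rests on Table 1's path.

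**2. Each cohort result against the text.**

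| Result | Cohort rules (2.3, 2.7.1) | MTD definition (of six) | Examples |
|---|---|---|---|
| 0 of 3 | escalate | not met | Table 2 escalates |
| 1 of 3 | add three patients | not met | – |
| 1 of 6 | nothing stated | met: stop | Table 1 goes on after six |
| 0 of 6 | escalate | met: stop | Table 1 goes on after six |
| 2 or more of 3 to 6 | de-escalate | not met | – |

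Table 1 has nine six-patient cohorts, 113 to 2,883 µg, each followed by a higher dose. Under the literal text each of them either meets the definition (0 or 1 DLT, stop) or requires de-escalation (2 or more). Table 1 therefore cannot occur as the rule is written. On the downward path, where a higher level has already failed and the lower one is filled to six, the definition works as it should.

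**3. Size.** The article gives no DLT rate, so the rate p is an assumption. Each cohort starts with three patients and goes to six after one DLT, with no further enlargement.

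- a = P(0 of 3) = (1 − p)³
- b = P(1 of 3, then 0 of 3) = 3p(1 − p)⁵
- k = standard-phase levels below 4,000 µg: 9 on Table 1's doses, 3 on Table 2's
- P(escalation ends before 4,000 µg is tested), if 1 of 6 permits escalation: 1 − (a + b)^k
- The same, if 1 of 6 stops: 1 − a^k

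At p = 0.05: a = 0.95³ = 0.857, b = 0.15 × 0.95⁵ = 0.116, a + b = 0.973.

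- Table 1 doses: 1 − 0.973⁹ = 0.215, against 1 − 0.857⁹ = 0.750.
- Table 2 doses: 1 − 0.973³ = 0.078, against 1 − 0.857³ = 0.370.

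The same formulas over a range of assumed rates:

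| DLT rate | Table 1: 1 of 6 escalates | Table 1: literal | Table 2: 1 of 6 escalates | Table 2: literal |
|---|---|---|---|---|
| 2% | 4% | 42% | 1% | 17% |
| 5% | 22% | 75% | 8% | 37% |
| 10% | 59% | 94% | 26% | 61% |

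A constant rate over a 35-fold dose range is crude. With a rate rising from 1% at 113 µg to 10% at 4,000 µg (logit linear in log dose), the Table 1 figures are 16% and 63%.

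**4. How often 1 of 6 decides the matter.** The chance that the first standard-phase cohort with any DLT lies below 4,000 µg and finishes at 1 of 6 is b(1 − a^k)/(1 − a). At 5% this is 0.116 × 0.750/0.143 = 0.61 on Table 1's doses and 0.116 × 0.370/0.143 = 0.30 on Table 2's.

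**The case against.** The best defence is that nobody would run the trial this way. The design is called a standard, rule-based 3 + 3; 'maximum' is part of the term being defined; and the safety review committee (SRC) sets each next dose with all adverse events and DLTs before it (sections 2.7.1 and 2.10). Section 2.7.1 points to Figure 2B for these rules. That flowchart is not available here and may show the step after 1 of 6. Table 1 itself shows the intended direction. All of this makes the conventional rule the probable intention, and under that rule the wording changes no dose. It does not repair the text: the SRC's discretion concerns the next escalation cohort, and section 2.7.1 says there is none once the MTD is defined.

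A reader might go further and infer that 0 of 3 already fixes the MTD, because the sentence in section 2.7.1 gives no denominator, and that Table 2 and the Discussion's 14th patient at 4,000 µg (4 + 9 + 1) are then contradicted too. The document does not support that. The sentence just before it concerns filling a level to six patients, the other two definitions name six, and section 2.3 expressly escalates after a cohort with no DLT. Table 2 never escalates from a six-patient cohort, so it agrees with the of-six definition.

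The 0-of-6 conflict is also weaker than the 1-of-6 one. On the way up it needs a cohort enlarged without a DLT, and there the specific no-DLT rule points to escalation.

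**Conclusion.** The point holds as a fault in a stated decision rule. The MTD is defined three times without 'highest', the definition ends escalation, the text gives no escalation instruction for 1 of 6, and the result contradicts Table 1, on which the totals of 63 and 77 rest. It should be corrected, although the conventional rule was probably meant.

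At an assumed constant 5% DLT rate, the literal rule raises the chance of fixing the dose below 4,000 µg, with that dose untested, from 22% to 75% on Table 1's doses and from 8% to 37% on Table 2's. These literal figures are the upper end and should not be read as the expected effect: they need an SRC that never escalates after 1 of 6. Every DLT rate is an assumption, and Table 1 is the longer of the two dose ladders.

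**What to change.** Use one definition in the abstract, section 2.3 and section 2.7.1: the MTD is the highest tested dose level at which no more than 1 of 6 DLT-evaluable patients has a DLT. Add one sentence to the cohort rules: 0 of 3, or at most 1 of 6, permits escalation unless the next level has already been found too toxic or 4,000 µg has been reached. Check that Figure 2B shows the same step.

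The cost is protocol wording only. No patients, visits or procedures are added, and the totals of 63, 19 and 77 stay as they are.
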